### This study

This paper describes the QUEST-CLC study (QUalitative and Effectiveness study to Select optimal Treatment for CLuster-C PD), a multicenter RCT comparing GST, IST, and TAU for Cluster-C PDs. The main objective of the study is to compare the relative (cost-) effectiveness of these three treatments. Based on previous research, superiority of GST to TAU is expected regarding PD symptom reduction. How GST compares to IST in (cost-) effectiveness is yet unclear. Although in GST larger numbers can be treated in less therapist time than with IST, it is not yet clear how this relates to respective treatment effects. It is hypothesized that GST does not perform worse than IST regarding symptom reduction. As the few previous studies on treatment for Cluster-C PDs that do exist are generally limited to symptom reduction, measures of quality of life, social, work, and other functioning are also included. Furthermore, this study intends to identify predictors and moderators that are relevant for optimal treatment allocation. With such moderators a tool for treatment recommendation will be created. The tool is based on an empirically derived subset of several variables hypothesized to correlate with therapy outcome (i.e., diagnoses, age, gender, ethnic background, socio-economic status, educational level; introversion, autistic traits, sleep problems, severity of childhood traumas).

In addition, two sub studies will be carried out. First, the treatment integrity of GST and IST will be evaluated and compared with TAU. Second, a qualitative study will be performed in which patients and therapists are interviewed. The aim is to obtain a thorough understanding of how the different therapies helped patients recover, what elements are pivotal to lead a fulfilling life, and to explore experiences for patients in the ST-arms, in order to improve ST for Cluster-C patients. Moreover, ST-therapists’ perspectives about treatment will be used to further improve treatment protocols (as was done in the pilot study [24, 25]).

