The power analysis is based on 9 sites, despite 10 sites intent to participate, because sites might withdraw or not reach the intended N. For feasibility purposes a larger N is intended for the GST condition, as more participants can be treated at the same time in a group. With minimal N’s of 162 (GST), 108 (IST) and 108 (TAU) power of pairwise comparisons GST-IST and GST-TAU is 90% at an adjusted p-level of .025 to detect an effect size of d = .44 at post-test (or follow-up). For the GST-IST comparison, we don’t have expectations about the direction of a possible difference, but the power is sufficient to detect a medium effect size. One potential issue is treatment dropout. For pairwise comparisons of GST with the other two arms power is 80% to detect an RR = 2.5 at adjusted p = .025, for instance when dropout is 25% from GST vs. 10% from IST). (G)LMM analysis for repeated measures will be used to account for correlations introduced due to grouping (at multiple levels) and compensate for potential loss of power due to treatment drop-out. This type of analysis usually has greater power compared to non-multilevel/non-repeated measures analyses, however an actual power calculation for multilevel analysis with repeated measures and multiple sites is very difficult if not impossible because of the many random effects of the to-be-estimated model.

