To derive a tool that informs future patients and therapists what treatment is likely to be most efficacious for the specific patient (personalized care), we currently plan to use the Personalized Advantage Index (PAI) procedure developed by DeRubeis [61]. The LMM model of the outcome analysis is the starting point. Then, potential predictors and moderators are derived by suitable predictive machine learning models. Two methods for model selection, best subset selection and Lasso regression, will be performed and validated using 10-fold cross validation, after which one of the two methods will be selected. The individual’s PAI and hence the advantage of optimal treatment allocation can be estimated with a leave-one-out procedure [61, 62]. However, the field of personalized treatment allocation is developing rapidly and other methods might turn out to be more accurate and robust than the PAI method. We will therefore use a method that is optimal given the state of affairs at the end of data collection.

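### As written, the treatment-selection tool chooses its predictors and method before leave-one-out is applied, so the estimated advantage of optimal allocation would be biased upward even with no true moderation

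*Protocol article*

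**What the plan says.** The tool is described in one paragraph of the Analyses section of the protocol article, as a sequence of steps:

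1. The linear mixed model of the outcome analysis is the starting point.
2. Next, "potential predictors and moderators are derived by suitable predictive machine learning models".
3. On how the model is chosen, the text reads: "Two methods for model selection, best subset selection and Lasso regression, will be performed and validated using 10-fold cross validation". The winner is settled at the end of this step: "after which one of the two methods will be selected".
4. The individual PAI is then obtained, and "hence the advantage of optimal treatment allocation can be estimated with a leave-one-out procedure".

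The section This study lists the candidate variables: "diagnoses, age, gender, ethnic background, socio-economic status, educational level; introversion, autistic traits, sleep problems, severity of childhood traumas". That is ten named items, and more once categorical ones are coded. The Analyses section also tests verbal intelligence as a predictor and moderator.

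The paragraph calls the PAI a current plan. It reserves the right to use whatever method is best when data collection ends, and sets no validation rule for such a replacement. The article mentions no held-out sample, and it does not say that selection is repeated when a patient is left out.

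**The concern.** Leave-one-out gives an honest estimate only if everything learned from the outcomes is relearned without the left-out patient. In the order given, the variables and the winning method are settled first. Leave-one-out then re-estimates the coefficients of a model whose form already reflects that patient's outcome. A chance interaction that survives selection will look useful in the patients who produced it.

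The 10-fold cross-validation does not repair this. It serves to choose between best subset and Lasso, and the advantage of allocation is not estimated on its held-out folds.

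At stake is the figure that would show whether matching patients to GST, IST or TAU helps. The Discussion presents the tool as support for patients and clinicians in choosing treatment. An inflated advantage could lend credit to a tool with no value.

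**Working it through.** **Plan's own figure.** The article gives no figure for the PAI or its advantage. The nearest is in Sample size: "power of pairwise comparisons GST-IST and GST-TAU is 90% at an adjusted p-level of .025 to detect an effect size of d = .44". It serves here only to fix the sample size. With 162 vs 108 and two-sided alpha .025 (sidedness is not stated, so this is assumed):

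- noncentrality = 0.44 × √(162 × 108 / 270) = 0.44 × √64.8 = 3.54
- power = Φ(3.54 − 2.24) = Φ(1.30) ≈ 90.3%; the noncentral t gives 90.0%

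The stated 90% is reproduced.

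**Simulation A, following the described steps.** Inputs:

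- From the article: 162 vs 108 patients; best subset and Lasso; 10-fold cross-validation; leave-one-out at the end; ten named candidates.
- Assumed: 10, 15 or 25 independent standard-normal candidates; outcome SD 1; three prognostic variables (coefficient 0.25 each); no treatment effect and no moderation; forward selection of up to eight interactions as a stand-in for best subset; all main effects kept; two arms at a time; no clustering or repeated measures; 300 trials per setting.

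Advantage = mean outcome of patients on their indicated arm − mean outcome of patients on the other arm. The true value is 0.

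Two pipelines were run on the same data:

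- *Sequential:* tune both methods by 10-fold cross-validation on all patients, keep the one with lower error, then refit only the coefficients by leave-one-out.
- *Nested:* repeat selection, tuning and method choice inside each of 10 outer training folds, and predict only the held-out patients.

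| Candidates | Sequential, mean (SE) | Nested, mean (SE) | Sequential, falsely significant | Nested, falsely significant |
|---|---|---|---|---|
| 10 | 0.077 (0.014) | 0.005 (0.009) | 16% | 4% |
| 15 | 0.116 (0.013) | 0.010 (0.009) | 22% | 7% |
| 25 | 0.108 (0.015) | 0.011 (0.009) | 24% | 4% |

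Falsely significant means a positive advantage with p < .05 in an ordinary two-sample t test, nominally 2.5% in that direction. The sequentially selected models, applied to fresh simulated patients, gave an advantage of 0.00 SD.

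Most of the bias comes from the 34-42% of null trials in which at least one moderator was selected. In those, the mean sequential advantage was 0.20, 0.24 and 0.25 SD, against 0.05, 0.08 and 0.04 SD for the nested estimate. For scale, 0.20 / 0.44 = 45% and 0.25 / 0.44 = 57% of the effect size on which the trial is powered.

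**Simulation B, a simpler selection rule.** With 12 independent candidates, interactions kept at |t| > 1.414 (an AIC-type rule), 162 vs 108 and 300 trials, full-sample selection plus leave-one-out gave 0.135 SD, with z > 1.96 in 23.3% of trials. Nested 10-fold gave −0.005 SD and 4.3%.

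The two rules differ, but both show upward bias that nesting largely removes. Nesting does not make an ordinary t test exact: 4-7% is still above the nominal 2.5%.

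**The case against.** The strongest reply is that full-sample selection is inferred. The article never uses those words, does not define what is refitted when a patient is left out, and cites sources for the procedure that are not at hand. A condensed article may leave nesting to a fuller plan. The paragraph is also openly provisional. This stands in part. A reader might infer that the plan commits to selecting on all patients and that the reported advantage will certainly be inflated. The text supports only the conditional statement that following its steps in the order given produces the bias. It is more than a missing detail, however. The article names the selection methods, the number of folds, the order and the estimator of benefit, and ties leave-one-out to the last step alone. The freedom to change method adds no safeguard.

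A reader might also infer that the whole third research question, on which patient characteristics predict better response, rests on this number. It does not. The Analyses section gives that question separate (G)LMM tests of predictor by treatment and predictor by time by treatment terms, which use neither the PAI nor leave-one-out.

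Finally, the magnitude depends on the simulation's assumptions, and the article plans no significance test of indicated against non-indicated treatment. The false-significance rates therefore illustrate how convincing a spurious result could look. They are not an error rate of a planned test.

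**Conclusion.** The point holds in conditional form. Followed in its written order, the tool's development gives an upward-biased estimate of the advantage of optimal allocation when no moderation exists. Under the stated assumptions the bias averages 0.077 to 0.135 SD, against −0.005 to 0.011 SD with nested selection. The direction was the same in every setting tried. The size would change with the number and correlation of candidates, the three-arm structure, clustering and repeated measures, so it should be read as illustrative.

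Only the tool's estimated benefit is affected. The GST-TAU and GST-IST comparisons and the (G)LMM moderator tests are not. The change should be made before the tool is built, but it does not touch the trial's main conclusions.

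**What to change.** State in the analysis plan that:

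- predictor and moderator selection, tuning and the choice between best subset and Lasso, with any standardisation, are repeated on the training patients only within each held-out fit, for example in repeated 10-fold outer cross-validation;
- the PAI and the advantage of optimal allocation are estimated only from the resulting held-out predictions;
- the same rule applies to any method that replaces the PAI.

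The final tool may still be fitted on all patients. The nested loop is there to estimate its benefit. If a test of that benefit is added, it should not be an ordinary t test on the cross-validated predictions.

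The cost is computing time and a few sentences of text. The reported benefit will probably be smaller. No data collection, randomisation or sample size changes.

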### Economic Evaluation

The economic evaluation will involve a combination of cost-effectiveness analysis (CEA) and cost-utility analysis (CUA). In a CEA, effects are presented in clinical outcomes (here the primary outcome is Cluster-C PD-severity decrease). The outcome for the CUA is Quality Adjusted Life Year’s (QALY’s), based on the EQ-5D-5L utility scores [46], and the MHQoL-7D [45] for a full description see above) primarily on Dutch utilities [63]. In the CUA, the Incremental cost-effectiveness ratio (ICER) will be expressed as incremental costs per QALY.

#### Cost measurement

For this study we have developed a cost interview especially designed for this group, based on existing questionnaires, such as the de Trimbos/iMTA questionnaire for Costs associated with Psychiatric Illness (TIC-P) [64]. Since PDs are known to interfere with all life aspects, this economic evaluation will be performed from a societal perspective, which implies that all relevant costs and outcomes are considered. Health costs covered intervention, healthcare, social work, emergency department, community health service, informal and alternative care. Costs outside the health care consist of comprised losses in productivity of (unpaid)work, study, and domestic activities up to two years, traveling costs, out-of-pocket costs (e.g., alcohol, tobacco, drugs, impulsive spending), and judicial costs. Costs are measured at baseline before random assignment to treatments, and every assessment for 2 years, using a 4-month recall period.

Total costs will be estimated using a bottom-up (or micro-costing) approach, where information on each element of service used is multiplied by an appropriate unit cost and summed to provide an overall total cost [65]. The valuation of healthcare, patient and family costs will be based on the updated Dutch manuals for cost analysis in healthcare research [66]. In brief, the manual recommends standardized cost prices for health care and shadow prices for informal care (meaning a standard cost price based on general hourly wages). Costs of transport will be calculated as the mean distance per destination multiplied by standard cost prices. Costs of medication will be calculated using prices based on Daily Defined Dosage (DDD) taken from the healthcare institute of the Netherlands^1^ indicating the mean medication usage per adult a day inclusive claw back (by the government-imposed discount for patients, paid by the pharmacy). Productivity losses will be calculated by means of the friction cost method, based on a mean added value of the Dutch working population. The friction costs method considers production losses confined to the period needed (usually 90 days) to replace a sick employee. In case of uncertainty, we will use a conservative estimation (i.e., the lowest cost price). Cost prices will be expressed in 2021 euros. If necessary, existing cost-prices will be updated to 2021 using the consumer price index (CPI). Interrater agreement of the cost interview will be assessed by blinded double coding.

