In total five assessments take place: at baseline (week 0), mid-treatment (week 17), post-treatment (week 34), poster booster (week 51) and a follow-up 2 years after baseline. For the GST-arm this corresponds to a mid-treatment after 15 sessions, post-treatment after another 15 sessions, post-booster after 4 booster sessions and follow-up a year after termination of the therapy. IST follows the same pattern of GST, except that this arm starts with sessions twice a week, resulting in a mid-treatment after 30 sessions. For the TAU-arm the assessments are planned at the same time points (i.e., weeks), but note that these times might relate to different phases of the treatment than with GST/IST. For an overview of the primary and secondary outcome measures per assessment see Table 1. When more than 2.5 months have passed between a baseline assessment and start of therapy, an extra pre-treatment assessment is conducted in order to have a more reliable baseline measurement. For those patients in need of a pre-treatment assessment, the period between baseline and pre-treatment can be used as a proxy for a waitlist condition in later analyses. If patients decide to stop treatment, we will first try to motivate them to continue in the assessments and otherwise try to plan an exit-assessment starting with the primary outcome measures. There is a small financial renumeration of 40 euro per patients when they have completed all assessments.

**Table 1 Tab1:** Overview of measures and assessment times

	Screening	Baseline	Pre-treatment	Mid-treatment	Post-treatment	Post-Booster	1 year Follow-up
SCID-5-S, SCID-5-P	•						
Screenings interview	•						
Biographical interview		•					
Demographics		•					
Severity index: AVPDSI/DPDSI/OCPDSI		•	•	•	•	•	•
Cost interview		•	•	•	•	•	•
PDBQ-69		•	•	•	•	•	•
RSES		•	•	•	•	•	•
MSGO		•	•	•	•	•	•
WHODAS 2.0		•	•	•	•	•	•
BSI		•	•	•	•	•	•
EQ-5D-5L & MHQoL-7D		•	•	•	•	•	•
Happiness Question		•	•	•	•	•	•
SMI-2		•	•	•	•	•	•
YSQ-SR		•	•	•	•	•	•
SLEEP-50		•	•	•	•	•	•
Introversion inventory		•	•	•	•	•	•
AQ-10		•					
CTQ-SF		•					
NLV		•					

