### Drop-out, deviation from the treatment protocol, and follow-up

Patients are free to leave the study at any given time for any reason. However, when a patient refuses to participate in the assessments, the experimental treatment condition (i.e., IST and GST) will no longer be offered due to limited capacity of ST-therapists on the participating sites. Therapist can (in consultation with the researchers) decide to remove patients from treatment (i.e., pushout) in serious cases (e.g. when a client repeatedly fails to show up for treatment or seriously impedes the treatment process for fellow group members). Sites are responsible to provide a suitable alternative in case of drop- or pushout. Reasons for early termination of the treatment will be closely monitored and registered by the researchers in order to report these reasons in future publications. Deviation from the treatment length according to the ST-protocols is allowed when patients show sufficient progress in earlier phases (e.g., patients can independently apply advanced techniques by themselves). In this case the therapist is free to skip sessions in the protocol and or end treatment early.

Following both ST-protocols, we advise patients not to start a new treatment in the follow-up period and to apply the learned techniques on their own. Of course, we do not prohibit anyone from seeking help during this period. For the TAU condition this recommendation often does not apply, as therapy might not be finished yet. After having completed the follow-up assessment, the former therapist discusses the results with the patient as this was done during active treatment. Together, the therapist and patient evaluate whether there is a need for further therapy. If needed the therapist helps the patient determine what kind of therapy is fitting and where the patient can go if this therapy is not available at the respective treatment site.

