### Cost-Effectiveness and Cost-Utility Analyses

A baseline analysis will be performed to examine the comparability of groups at baseline for both costs and outcomes. We aim to use the multiple imputation method to handle missing values at item level using the individual mean score [67]. However, we will monitor recent developments in the rapidly advancing field of cost-effectives studies to decide on the most fitting technique when time is due. If necessary, methods are applied to control for differences in baseline [68]. The ICER will be determined based on incremental costs and effects of group-ST compared to TAU. The cost-effectiveness ratio will be stated in terms of costs per outcome rate, the cost-utility ratio will focus on the net cost per QALY gained. The ICER will be calculated as follows. ICER = (Ci – Cc) / (Ei – Ec), where Ci is the annual total cost of the GST, Cc is the annual total cost of TAU (resp. IST), Ei is the effect at 2-years follow-up for GST and Ec is the effect at 2-years follow-up for TAU (resp. IST). The three arms will be mutually compared, with a primary interest in the GST-TAU and the GST-IST comparisons. However, the IST-TAU difference will also be tested. The robustness of the ICER will be checked by non-parametric bootstrapping. Bootstrap simulations will also be conducted to quantify the uncertainty around the ICER, yielding information about the joint distribution of cost and effect differences. The bootstrapped cost-effectiveness ratios will be subsequently plotted in a cost-effectiveness plane, in which the vertical line reflects the difference in costs and the horizontal line reflects the difference in effectiveness. The choice of treatment depends on the maximum amount of money that society is prepared to pay for a gain in effectiveness, which is called the ceiling ratio. Therefore, the bootstrapped ICERs will also be depicted in a cost-effectiveness acceptability curve showing the probability that group-ST is cost-effective using a range of ceiling ratios.

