Another point of attention for multicenter studies is to organize and coordinate all participating sites in a clear manner. Maintaining the quality of the study protocol over 10 sites is a demanding task which requires considerable work and effort. The two junior researchers are the central figures of the study and keep in close contact with the local research assistants and coordinators of all sites. They oversee the daily coordination of the study, prepare the meetings, monitor the progress of the study and its legal, ethical and ICT aspects. Monthly meetings are held with all site coordinators to discuss the implementation of the study and to address potential difficulties. In addition, every six months the study board (site coordinators, experience experts, project leaders, the statistician and economical expert) gather to discuss developing and setting up new components to the study protocol. Finally, we (i.e., project leaders and junior researchers, independent of the sponsor) plan on auditing every site once during the inclusion period. After that, auditing will be conducted using a risk-based approach at sites who show higher rates of dropout, lower inclusions, less accuracy in assessments etc.

As previously stated, this trial consists of an extensive economic evaluation. To express the effects of the intervention we have chosen to include a cost-effectiveness and a cost-utility analysis to explore both PD-specific improvements as QALY’s. Moreover, we have chosen to incorporate two measurements to explore quality of life: the commonly used EQ-5D and the relatively new MHQoL-7D. While the EQ-5D is dominated by physical (somatic-medical) aspects of quality of life, the MHQoL-7D focusses more on mental aspects of quality of life (e.g., mood, self-image, future perspectives etc.) making it especially relevant for this population. Incorporating both questionnaires will give us an interesting opportunity to compare these measures for their suitability for a mental health population. For the economic evaluation we have chosen a time horizon of two years covering the one-year treatment and a follow-up period of one year. Although ideally one would want to choose a time horizon to cover all long-term costs and consequences (i.e., up to a lifetime), this relatively lengthy period gives the opportunity to explore the most essential period of change.

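### The 4-month cost recall leaves about weeks 51 to 87, a third of the two-year economic horizon, outside every cost interview, in a period when TAU and schema therapy use are expected to differ

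*Protocol article*

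**What the plan says.** All references are to the Protocol article.

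- **Recall.** Cost measurement: "Costs are measured at baseline before random assignment to treatments, and every assessment for 2 years, using a 4-month recall period".
- **Schedule.** Assessments: "In total five assessments take place", namely "at baseline (week 0), mid-treatment (week 17), post-treatment (week 34), poster booster (week 51) and a follow-up 2 years after baseline". Table 1 lists the cost interview at each of these and at an extra pre-treatment assessment, which is held only when more than 2.5 months pass between baseline and the start of therapy. It shows none between post-booster and follow-up.
- **Horizon and perspective.** Discussion: "For the economic evaluation we have chosen a time horizon of two years covering the one-year treatment and a follow-up period of one year". Cost measurement adds that "this economic evaluation will be performed from a societal perspective, which implies that all relevant costs and outcomes are considered". Total cost is to be built bottom-up, from volumes used times unit prices.
- **Cost term of the ICER.** Cost-Effectiveness and Cost-Utility Analyses sets a yearly cost ("where Ci is the annual total cost of the GST", and likewise for the comparator) against the effect at 2 years. It does not say how the yearly figure is formed.
- **Care in the second year.** Drop-out, deviation from the treatment protocol, and follow-up reports that patients in both schema therapy arms are advised against starting another treatment during follow-up, though nobody is barred from seeking help. It continues: "For the TAU condition this recommendation often does not apply, as therapy might not be finished yet".

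**The concern.** The recall window suits the 17-week spacing of year 1 but is kept for a final interval about three times as long. Volumes that nobody is asked about cannot enter a bottom-up total, so the two-year societal cost is observed for only about two thirds of its horizon.

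The gap may not affect the arms equally. TAU therapy that runs past week 51 and stops before about week 87 is seen by neither the week-51 nor the 2-year interview. If the last window is carried backward over the gap, that therapy is still missed, because it has already ended when the window opens. GST versus TAU is the primary economic comparison, and cost-effectiveness is part of the trial's main objective. The primary clinical outcome is not affected.

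**Working it through.** **Inputs.** Recall of 4 months (Cost measurement). Post-baseline cost interviews at weeks 17, 34, 51 and 2 years, taken as week 104 (Assessments, Table 1). Horizon of two years (Discussion).

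**Step 1: recall in weeks.** 4 months = 365.25 / 7 / 3 = 17.39 weeks.

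**Step 2: windows.** An interview at week t covers t − 17.39 to t.

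| Interview | Weeks covered |
|---|---|
| 17 | 0 to 17 |
| 34 | 16.6 to 34 |
| 51 | 33.6 to 51 |
| 104 | 86.6 to 104 |

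**Step 3: gap.** Weeks 0 to 51 are fully covered. The gap runs from week 51 to 104 − 17.39 = 86.6, which is 35.6 weeks. That is 35.6 / 104 = 34.2% of the horizon, and 35.6 / 53 = 67% of the time after week 51.

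**Step 4: check without converting to weeks.** 4 post-baseline interviews × 4 months = at most 16 of 24 months. At least 8 months, one third, remain uncovered.

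**Step 5: variations.**

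- With a recall of exactly 17 weeks the gap is weeks 51 to 87: 36 weeks, 34.6%.
- For GST the last assessment is also described as "follow-up a year after termination of the therapy". Moving it to week 102 or 103, and varying the recall from 16 to 18 weeks, gives 33 to 40 uncovered weeks (32% to 39%).
- If the year-1 visits are counted from a therapy start 5 or 10.9 weeks after baseline and the last stays at week 104, the total is 35.2 weeks (33.9%), part of it moved to the first weeks.
- In the 10.9-week case (2.5 months' wait), an extra pre-treatment cost interview would cover those first weeks. The remaining gap is then weeks 61.9 to 86.6, or 24.7 weeks. This applies only to patients who have that extra interview.

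**Step 6: what would close it.** At the existing last visit, the recall would have to reach back 104 − 51 = 53 weeks, about 12.2 months.

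**Step 7: does the article fill the gap another way?** The imputation it describes is for missing items within a questionnaire, not for a period that no questionnaire covers. The sensitivity analysis varies prices and volumes between minimum and maximum, but for these weeks the interview supplies no volume to vary. The friction-cost limit (usually 90 days) caps some paid-work losses and leaves health care, informal care and out-of-pocket costs untouched. No longer recall at the last visit, cost diary, registry source or interpolation is mentioned.

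**The case against.** The arithmetic is hard to dispute. The stronger case is against what a reader might infer from it.

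- **That the arms differ most in the gap.** No costs by period are given. The one cost contrast stated, GST delivery at about 50% of IST (Discussion), arises mainly in the treatment year, which the interviews cover. Only an expected difference in follow-up is supported.
- **That every comparison is affected alike.** The stated mechanism concerns TAU. GST and IST patients get the same advice for follow-up, so it does not reach GST-IST, although that comparison is equally incomplete.
- **That nothing can recover the missing volumes.** The Discussion mentions questionnaires that register the TAU provided, and Assessments mentions a treatment-related part of the cost interview handled by the non-blind assistant. Either might recover some therapy volume. Their timing and use for costing are not stated, and the TAU registration is not described as covering productivity, informal care or other societal costs.
- **That the estimate is biased whatever is done.** Interpolating between the windows at weeks 34 to 51 and 87 to 104 is a third option besides omission and carrying backward. Patients in the schema therapy arms may also seek help in these weeks, and that too goes unseen. Neither direction nor size of bias is shown.
- **That the bias can be priced.** Multiplying the Background's EUR 12,000 to 13,500 per person-year (2007 prices) by 36/52 gives about EUR 8,300 to 9,300. That is a total per patient. The ICER uses the difference between arms, and costs common to both cancel.

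It can also be said that a full protocol or analysis plan, not shown, may set out how unobserved intervals are valued, and that the missing-data technique is deliberately left open. That stands for the choice of method. It does not answer the point about collection: recall and schedule are fixed in this article, and an analysis rule cannot supply answers to questions that were not asked.

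**Conclusion.** The point holds in this form. On the stated schedule and recall, about 36 of 104 weeks (33 to 40 under the timing and recall variants, less for patients with the extra pre-treatment interview) lie outside every cost interview, with no stated way to fill them. Because TAU may continue while schema therapy patients are advised against new treatment, the GST-TAU and IST-TAU cost differences are at risk of bias. If TAU care in the gap is the larger omission, TAU cost is understated. How large the effect would be cannot be derived from the article.

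This assumes that the 4-month recall applies at the 2-year interview, as the article says without exception, and that no source outside the article supplies costs for these weeks. How much of the horizon has to be summed also depends on what the yearly cost in the ICER means, which the article leaves unexplained beside its two-year horizon. The consequence is confined to the economic evaluation, but that carries half of the first two research questions.

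**What to change.** 1. At the existing 2-year cost interview, ask about major, memorable items since the post-booster assessment: therapy, admissions and day treatment, work absence, informal care.
2. Take treatment sessions for weeks 51 to 104 from site records, in the same way in all three arms. Treatment-related questions can stay with the non-blind assistant, so that rater blinding is kept.
3. Keep the 4-month recall for small items. State in advance that their costs are interpolated between the week 34-51 and week 87-104 windows, and add a sensitivity analysis on that assumption.
4. State how the annual total cost in the ICER relates to the two-year horizon.

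This adds no visit. It needs a small amendment to one interview, before the 2-year interviews are held, and an extract of session records from the sites. The price is more recall error over about 12 months and a few extra minutes per patient.
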